Insulin	Healthy: Binding to insulin receptors on vascular endothelium → increased eNOS phosphorylation → ↑ NO release	Microvascular dilatation, ↑ MBV
	Obesity/type 2 diabetes: Binding to insulin receptor on vascular endothelium → activation mitogen-activated protein kinase pathway → ↑ production of ET-1	Vasoconstriction, ↓ MBV
Adenosine	Binding to A1, A2A, A2B, and A3 receptors on smooth muscle cells and endothelial cells → ↑ NO release	Microvascular dilatation, ↑ MBF
Acetylcholine	Healthy: Binding to muscarinic (M3) receptors on vascular endothelium → ↑ Ca^2+^ binding to eNOS → ↑ NO release	Vasodilatation
	Endothelial dysfunction: Binding to muscarinic (M2 and M3) receptors on smooth muscle → ↑ Ca^2+^ in smooth muscle	Vasoconstriction

*MVO2, myocardial oxygen consumption; NO, nitric oxide; MBV, myocardial blood volume; ET1, endotelin-1; MBF, myocardial blood flow*.

These microvascular effects of insulin are impaired in insulin-resistance, diabetes mellitus, obesity and hypertension, all common comorbidities in INOCA patients (25). Moreover, resistance to insulin's microvascular action can be a hidden phenomenon since it can occur before hyperglycemia, and thus overt metabolic defects (26). The effects of hyperinsulinemia on MBV and MBF have never been studied in INOCA patients, while the blunted effect of insulin on the coronary microcirculation can be an additional factor leading to endothelial dysfunction in INOCA.

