## Methods

### Overview

The MICORDIS trial is a single-center observational cross-sectional cohort study, comparing MBV in INOCA patients with a group of matched healthy controls (https://www.trialregister.nl/, unique identifier NTR7515). The trial will be performed at the Amsterdam University Medical Centers (UMC), location VU medical center. The study has been approved by the institutional ethics committee on human research of the Amsterdam UMC and carried out in compliance with the Declaration of Helsinki and in accordance with the Medical Research Involving Human Subjects Act (WMO).

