### Patient Enrollment

Patients with long-standing angina, documented non-obstructive CAD and lack of response to medical therapy will be included in the study. Non-obstructive CAD is defined as signs and symptoms of myocardial ischemia and ≤50% stenosis on coronary angiography and/or fractional flow reserve (FFR) >0.80. Signs and symptoms of ischemia are defined as; (1) stable chronic (i.e., several weeks or longer) symptoms suggesting IHD, such as chest discomfort with classic (i.e., angina pectoris) and/or atypical features regarding location, intensity and provoking factors, and 2) with or without objective evidence for myocardial ischemia on ECG or a cardiac imaging study (e.g., transthoracic echocardiography (TTE), nuclear imaging or CMR) at rest or during stress induced by exercise, mental or pharmacological triggers. After informed consent is obtained, eligible candidates meeting the selection-criteria listed in Table 3, will be enrolled.

**Table 3 T3:** Inclusion and exclusion criteria patient and control group.

Inclusion criteria	Age > 40 years
	Signed informed consent
	Stable and chronic symptoms suggesting ischemic heart disease^*^
	No CAD on coronary angiography: coronary stenosis ≤ 50% and/or FFR >0.80^*^
Exclusion criteria	Age > 80 years
	Use of medication^#^
	Pregnancy
	History of coronary revascularization (e.g., PCI or CABG)
	History of CAD, or ASC (e.g., myocardial infarction and unstable angina pectoris)
	History of stroke
	History of cardiac arrhythmia's
	History of heart valve disease
	Left ventricular dysfunction (i.e., LVEF <35%)
	Congenital heart disease
	Insulin-dependent diabetes mellitus
	Extensive comorbidities (i.e., cancer, other chronic diseases)
	Impaired renal function, defined as creatinine > 100 and eGFR <30
	Symptomatic asthma or chronic obstructive pulmonary disease
	Known allergic reaction to contrast agent
	Insufficient echocardiographic imaging quality
	Contra-indications for CMR (e.g., severe claustrophobia, metal implants, severe renal failure, severe asthma and known hypersensitivity for gadolinium)
	Contra-indications for microbubble usage (e.g., right-to-left shunt, severe pulmonary hypertension, uncontrolled hypertension and adult respiratory distress syndrome)
	Contra-indications for adenosine usage (e.g., hypersensitivity to active substances, second or third degree atrio-ventricular block, sick sinus syndrome, long QT syndrome, severe hypertension, concomitant use of dipyridamole)

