### Study Protocol

#### Screening

Study candidates will be identified at the outpatient cardiology clinic by active screening, while the control group is recruited by posters and advertisements in local media. Eligible subjects receive an information letter containing information about background, timeframes and risks of the study. Since subjects receive specific instructions regarding their eating habits and medication adjustments may be required prior to their first visit, informed consent is obtained before the first visit. The control group is matched to the patients with respect to sex and age, and are screened for exclusion criteria using TTE, electrocardiography (ECG), and laboratory tests to exclude severe heart disease and impaired renal function.

The study protocol is executed on two separate days (Figure 1). On day A, INOCA patients will undergo a CAG with ICFT to identify patients with epicardial and/or microvascular spasm and/or CMD. Patients and controls will undergo a stress CMR scan, including quantitative perfusion imaging and T1-mapping. Furthermore, all study-participants receive questionnaires including the Seattle Angina Questionnaire (SAQ), Hospital Anxiety and Depression scale (HADS), Perceived Stress Scale (PSS) and Pittsburg sleep quality index (PSQI) to assess angina-burden and mental-health status. Also sex-differences are investigated within groups. The women in the study will also receive a female-specific questionnaire developed for the Heart-study by the UMC Utrecht (33). This questionnaire includes specific questions about menstruation, pregnancy and postmenstrual phase. On day B both study groups will undergo myocardial contrast echocardiography (MCE) to examine MBV, an microvascular function test using the EndoPAT (Peripheral Artery Tonometer, Itamar Medical, Israel) for noninvasive assessment of microvascular function. Blood is collected and used to determine circulating endothelial colony forming cells (ECFC's) which represent endothelial precursors cells and contribute to *de novo* blood vessel formation *in vivo* (34). Circulating endothelial cells are established markers for endothelial damage, and may therefore also be used to identify biomarkers for INOCA (35). A smaller sample of blood is stored and frozen for future experiments. All analyses of non-invasive imaging are performed by an investigator blinded to the results of the ICFT.

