## Statistical Analysis and Sample Size Calculation

The expected effect size was estimated based on a study of Rinkevich et al. (52). Rinkevich compared the MBV between healthy controls and patients with Syndrome X using dipyridamole as a stimulus of MBV. A reduced MBV in non-obstructive CAD patients compared to healthy controls is the primary endpoint of our study. We expect the difference in MBV to be greater during stimulation with insulin and dobutamine, compared to dipyridamole as stimulus on MBV, making the data of Rinkevich appropriate for the use of sample size calculations. To detect a mean difference in MBV of 25 (MBV determined with MCE is dimensionless), we calculated a sample size of 24 patients per group to achieve a power of 80%, assuming a standard deviation of 30 in both groups. This calculation assumed the 5% significance level, using a two-sided independent sample *t*-test. To account for a projected dropout of 15%, the study population consist of 28 INOCA patients (14 males and 14 females) and 28 healthy controls (14 males and 14 females). The primary analyses of the study consist of a comparison of MBV at baseline, during hyperinsulinemia and during increased MVO2, and will be corrected for multiple testing using the Bonferroni method. Based on the distribution of continuous outcomes, independent samples *t*-test or Mann–Whitney *U* test are used as appropriate.

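### Controls are matched on sex and age, but the stated primary test leaves both out; this costs precision, and a comorbidity sensitivity model is advisable

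*Protocol article*

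**What the plan says.** Methods, Overview, describes the study as "comparing MBV in INOCA patients with a group of matched healthy controls". Study Protocol, Screening, names the matching factors: "The control group is matched to the patients with respect to sex and age". It does not say whether matching is individual or by frequency. Statistical Analysis and Sample Size Calculation sets equal sex quotas of 14 men and 14 women in each group.

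The same section bases the sample size on an unpaired test: "This calculation assumed the 5% significance level, using a two-sided independent sample" t-test, with "To detect a mean difference in MBV of 25" and a standard deviation of 30. The primary comparisons are MBV at baseline, during hyperinsulinemia and during increased oxygen consumption, and they "will be corrected for multiple testing using the Bonferroni method". The test is then fixed: "Based on the distribution of continuous outcomes, independent samples" t-test or Mann-Whitney U test. No covariate, stratum or pair term is named.

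On comorbidity, the Background (after Table 2) says: "These microvascular effects of insulin are impaired in insulin-resistance, diabetes mellitus, obesity and hypertension, all common comorbidities in INOCA patients". Table 2 lists insulin as raising MBV in health and lowering it in obesity or type 2 diabetes. Table 3 lists "Use of medication" as an exclusion, and its footnote restricts this to the control group. Among the forms of diabetes, Table 3 names only the insulin-dependent form as an exclusion.

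**The concern.** There are two separate issues.

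**Precision.** Matching makes the two groups alike on sex and age. A two-sample test that leaves those factors out still counts their contribution to MBV as random error, so its standard error is too large by whatever share of variance they explain. With 24 analysable people per group and a Bonferroni correction over three tests, even a moderate gain in precision would be useful.

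**Interpretation.** Conditions that the article itself links to the response to insulin are allowed in patients, while controls must be free of medication. Drug-treated hypertension or diabetes can therefore occur in patients only. A lower MBV in patients, above all during hyperinsulinemia, may partly reflect these conditions, and the stated primary analysis gives the reader no way to see how much.

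**Working it through.** **Inputs from the article.** Difference 25, SD 30, so d = 25/30 = 0.833; 24 per group; two-sided 5%; three Bonferroni comparisons, so 0.05/3 = 0.0167 each.

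**Inputs not in the article, assumed as ranges.** R², the share of MBV variance explained by age and sex; the within-pair correlation rho; the prevalence and effect of comorbidity.

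**1. The plan's own figure.** An exact two-sample t calculation at 5% gives 23.6, hence 24 per group, with power 80.7% at 24. The stated sample size reproduces. At 0.0167 the same 24 per group give 65.6%, which is the baseline below. That this is under 80% comes from sizing at 5% while testing at 0.05/3. It is a different matter and is not caused by the missing covariates.

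**2. Adjustment for age and sex.** Residual SD = 30 × √(1 − R²), so d becomes 0.833/√(1 − R²).

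| R² (assumed) | Residual SD | d | Power at 0.05 | Power at 0.0167 |
|---|---|---|---|---|
| 0 | 30.0 | 0.833 | 80.7% | 65.6% |
| 0.1 | 28.5 | 0.878 | 84.6% | 71.0% |
| 0.2 | 26.8 | 0.932 | 88.5% | 76.8% |
| 0.3 | 25.1 | 0.996 | 92.2% | 82.8% |

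These figures use 48 − 2 = 46 degrees of freedom. Charging the two covariates leaves 44 and lowers each power at 0.0167 by less than 0.2 percentage points.

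**3. The unadjusted test on matched data.** The 65.6% gives the planned test no credit for the balance that matching creates. A simulation of 24 matched pairs (100,000 runs) gives, for the independent t-test:

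| rho (assumed) | True type I error at nominal 5% | Power at 0.0167 |
|---|---|---|
| 0 | 5.1% | 65.7% |
| 0.1 | 3.9% | 66.6% |
| 0.2 | 2.9% | 67.2% |
| 0.3 | 2.0% | 68.2% |

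The test never rejects too often (5.1% at rho = 0 is simulation error around 5%). If matching on age and sex were perfect and they were the only source of within-pair correlation, rho would equal R². The gain from adjustment would then be 71.0 − 66.6 = 4.4, 76.8 − 67.2 = 9.6 and 82.8 − 68.2 = 14.6 points, a little less than the comparison with 65.6% suggests.

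**4. A strict paired test is not a free alternative.** If 15% drop out independently on each side, 28 × 0.85 × 0.85 = 20.2 pairs stay intact. With 20 pairs, paired power at 0.0167 is 56.9%, 62.9% and 69.7% for rho = 0.1, 0.2 and 0.3. A model with age and sex as covariates loses nobody in this way.

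**5. Comorbidity, as an illustration only.** Suppose no group difference apart from comorbidity. Spurious difference = (prevalence difference) × (effect in SD) × 30.

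- Low end: 0.2 × 0.3 × 30 = 1.8 units, which is 1.8/25 = 7% of the target difference; rejection rate 1.9% at 0.0167.
- High end: 0.6 × 0.8 × 30 = 14.4 units, which is 14.4/25 = 58% of the target; rejection rate 22% at 0.0167.

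Both factors are assumed. The range runs from negligible to material, and the article does not say where in it the study lies.

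**The case against.** A reader might infer that the matching is wasted or the test invalid. Neither follows. Matching limits age and sex confounding whichever test is used, and the unpaired test errs only on the cautious side. Individual pairs are never stated, and the sex quotas fit frequency matching equally well, so a paired test cannot be called the required analysis. Every value of R² and rho here is assumed. All of this stands, and it limits the point to precision.

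A reader might also object to testing three conditions, measured in the same people, as separate two-sample problems. That is not an error: Bonferroni is valid under any dependence between the tests. One mixed model over the three conditions would be a preference, and a simple random intercept would impose equal variances and correlations that nothing in the article supports.

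The strongest temptation is to say that the primary result must be corrected for comorbidity. The documents do not support this. The stated aim is whether MBV is lower in INOCA patients, which is a group difference. The Abstract derives the hypothesis partly from diabetes and obesity as INOCA-related conditions, and the Background treats blunted insulin action as a possible contributor to INOCA. Adjusting for them could remove part of the mechanism under study. Table 3 also excludes uncontrolled hypertension and extensive comorbidity in both groups, and the secondary objectives compare risk factors between groups and MBV by insulin resistance. Those comparisons do not adjust the primary result, but they show that the issue was not ignored.

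Finally, covariates and sensitivity models are often left to a full protocol or analysis plan that is not shown. That would answer a complaint about silence. It does not answer the first half of this point, because the article names the test.

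**Conclusion.** The point holds in a limited form. The article fixes an unadjusted two-sample test for a design matched on sex and age. The consequence is a conservative test and lost precision, not a false-positive risk. Against 65.6% at alpha 0.05/3 with 24 per group, adjustment would give about 71%, 77% or 83% if age and sex explain 10%, 20% or 30% of MBV variance, and practically nothing if they explain little. These figures rest on the article's difference of 25 and SD of 30 and on the assumed R².

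The comorbidity issue is separate and has its textual basis in the Background, Table 2 and Table 3. It bears mainly on the hyperinsulinemia comparison, since the article's statement concerns the response to insulin. It supports a pre-stated sensitivity analysis and careful wording, and does not call for replacing the primary result.

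**What to change.** 1. State whether matching is individual or by frequency.
2. At each of the three conditions, compare the groups with a linear model for MBV (transformed if skewed) containing group, age and sex. Keep the Bonferroni correction. If matching proves to be individual, a pair term may be used instead, allowing for broken pairs.
3. Pre-state one supportive sensitivity model that adds recorded risk factors, for example BMI, blood pressure and diabetes status. Say in advance that overlap between the groups may be limited, that medication cannot be separated from group because controls have none by design, and that some covariates may lie on the causal path.
4. Word the conclusion as an association with INOCA whatever the supportive model shows. The design is cross-sectional and observational, so agreement between the models would not justify stronger language.

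The cost is a change of analysis wording and two degrees of freedom in each primary model. Sex and age must be known for matching. The article plans to compare baseline characteristics and cardiovascular risk factors but does not list BMI or diabetes status by name, so their recording should be confirmed. Trial Status reports eight patients and three controls enrolled, so at that stage the change could still be made before most of the data exist.

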## Conclusion and Implications

To summarize, the MICORDIS study is a single-center, observational cross-sectional cohort trial to study the change in MBV in INOCA patients at baseline, during hyperinsulinemia and hyperemia. This is the first study that incorporates a range of ICFT and advanced non-invasive imaging methods to assess MBV and associated pathophysiological mechanisms in INOCA patients. This study may provide novel insight into the pathophysiological and diagnostic process of microvascular coronary dysfunction, which are of great importance in a comprehensive and effective treatment of INOCA patients.

## Trial Status

Currently including patients. Currently enrolled eight patients and three matched healthy-controls.

## Data Availability Statement

The raw data supporting the conclusions of this article will be made available by the authors, without undue reservation.

## Ethics Statement

The studies involving human participants were reviewed and approved by Medisch Ethische Toetsingscommissie VUmc OZW O8A-08 | [name]. The patients/participants provided their written informed consent to participate in this study.

## Abbreviations

ΔMBV: Capillary recruitment
CAG: Coronary angiography
CFR: Coronary flow reserve
CFVR: Coronary flow velocity reserve
CMD: Coronary microvascular dysfunction
CMR: Cardiac magnetic resonance
COVADIS: Coronary Vasomotor Disorders International Study
CRT: Coronary reactivity testing
ECFCs: Endothelial colony-forming cells
ECG: Electrocardiogram
ET-1: Endothelin-1
FFR: Fractional flow reserve
HADS: Hospital Anxiety and Depression scale
HE: Hyperinsulinemic-euglycemic
HMR: Hyperemic microvascular resistance
ICFT: Intracoronary function test
IMR: Index of microcirculatory resistance
INOCA: Ischemia with non-obstructed coronary arteries
LAD: Left anterior descending coronary artery
MACE: Major adverse cardiac events
MBF: Myocardial blood flow
MBV: Myocardial blood volume
MCE: Myocardial contrast echocardiography
MFV: Microvascular flow velocity, MI, Mechanical Index
MOLLI: Modified look-locked inversion
MPRi: Myocardial perfusion reserve index
MR: Microvascular resistance
MVO2: Myocardial oxygen consumption
NO: Nitric oxide
Pd: Distal coronary pressure
PET: Positron emission tomography
PSQI: Pittsburg sleep quality index
PSS: Perceived Stress Scale
RCA: Right coronary artery
SAQ: Seattle Angina Questionnaire
TTE: Transthoracic echocardiography
WMO: Medical Research Involving Human Subjects Act (in Dutch: Wet Medisch-wetenschappelijk Onderzoek met Mensen).
